**Hypothesis 1a) Children’s health and development outcomes**			
*Cognitive development*			
Bayley scales of infant and toddler development III (BSID)^a^	X	X	
Wechsler preschool and primary scale of intelligence (WPPSI) – Valid for ages 2.6-7.3^b^		X	X
*Language and socio-emotional development*			
Peabody Picture Vocabulary – Valid for ages 2 + ^c^		X	X
Child health questionnaire – Valid for ages 5+; Measures functional health and well-being^d^		X	X
Expressive Vocabulary Test		X	X
Longitudinal Study of Australian Children (LSAC) questions – Items on health status, injury and hospitalisation, health care access and affordability	X	X	X

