**Hypothesis 1b) Children’s academic achievement and ability**			
Woodcock Johnson NU tests – Literacy and numeracy^e^			X
Devereux Early Childhood Assessment Program (DECA) – 37 observer rated positive behaviour items (subscales are initiative, self-control and attachment)^f^	X	X	X

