**Hypothesis 1c) Children’s emotional and behavioural regulation**			
Greenspan socio-emotional growth chart (SEGC) – 35 item measure of socio-emotional milestones for ages 0–42 months^g^	X		
Brief infant toddler social emotional assessment (BITSEA) – 42 item parent completed screener for social-emotional/behavioural problems for ages 12–36 months^h^	X	X	
Child behaviour checklist – Identifies behavioural problems; Valid 18+ months^i^		X	X
Alarm baby distress scale (ADDB) – Social and interactive behaviour of infant in interaction with researcher; Valid for ages 1–36 months^j^	X		

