**Hypothesis 2 Incidence of poor parenting**			
*Parent–child relationship*			
Strange situation procedure (SSP) – Conducted in an unfamiliar toy-filled room consisting of a structured sequence of brief episodes of separations and reunions from primary caregiver; Valid for 8–30 months^k^	X	X	
Story stem assessment – Uses dolls and narrative to measure the child’s representations of their attachment relationships; Valid for ages 3+ years^l^		X	X
Emotional availability scale (EAS) – 20 minutes free play between child and mother, coded for adult sensitivity, structuring, non-intrusiveness, non-hostility and child’s responsiveness; Valid for ages 0–7 years^m^	X	X	X
*Parenting, stress and attitudes*			
Home observation measurement of environment (HOME)–Semi-structured interview and direct observation of home environment by trained assessor to measure parent responsiveness and acceptance of the child, organisation of the environment, learning materials, parental involvement, variety of experience^n^	X	X	X
The parenting daily hassles scale – 20 items where parents rate the frequency and intensity/impact of experiences that can be a ‘hassle’ to parents^o^	X	X	X
Longitudinal Study of Australian Children (LSAC) Parenting Practices: Parent self-efficacy and harsh parenting scales	X	X	X
K6 – Measures non-specific psychological stress in adults^p^	X	X	X
Rand depression screener – 8 item self-report that screens for depressive and dysthymic disorders^q^	X	X	X
Longitudinal Study of Australian Children (LSAC) questions – Items on use of health and welfare services, employment and experience of neighbourhood	X	X	X

Notes for Table 1:

^a^Bayley N: *Bayley Scales of Infant and Toddler Development.* 3^rd^ edition. New York: The Psychological Corporation – Harcourt Brace Jovanovich; 2006.

^b^Wecshler D: *Wecshler Preschool and Primary Scale of Intelligence*. 3^rd^ edition. San Antonio TX: PsychCorp; 2004.

^c^Dunn L, Dunn D: *Peabody Picture Vocabulary Test*. San Antonio TX: PsychCorp; 2007.

^d^Waters E, Salmon L, Wake M, Wright M, Hesketh K: *Child Health Questionnaire Australian. Authorised Adaption of the Child Health Questionnaire*. Melbourne: Royal Children’s Hospital.

^e^Woodcock RW, McGrew KS, Mather N: *Woodcock-Johnston III*. Itasca IL: Riverside Publishing; 2001.

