### Data analysis

The data analysis will identify the impact of ‘Intention to treat’ at the level of the individual child. The analysis will compare the change in an outcome measure (at time of data collection minus at baseline) for children in the intervention group with children in the control group. Impact evaluations will be conducted on outcomes measures after the 12, 24 and 36 month data collections as well following the data collection after the commencement of the first year of schooling.

For comparisons between the randomised intervention and control groups from the trial it should be possible to estimate the program impact as the difference in mean outcomes between those groups. For continuous outcome variables this will be the difference in mean changes in the outcome between intervention and control groups. For categorical outcome variables it will be differences in the change in the proportions of children in each category between intervention and control groups. For comparisons between the EYEP intervention group and the control group from LSAC a quasi-experimental matching method (difference-in-difference) will be used. Statistical significance will be established via t-tests for individual outcomes or Hotelling T tests for groups of outcomes.

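### Impact is defined as change from baseline for every outcome, but 7 of the 19 instruments with follow-up have no entry assessment, so that estimate cannot be computed for them

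*Protocol article*

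**What the plan says.** The Data analysis section of the protocol article defines impact as a change: "The analysis will compare the change in an outcome measure (at time of data collection minus at baseline) for children in the intervention group", compared with the control group. It applies this to the 12, 24 and 36 month collections and to the school collection.

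The second paragraph says that "it should be possible to estimate the program impact as the difference in mean outcomes between those groups". It then spells this out by type of variable: "For continuous outcome variables this will be the difference in mean changes in the outcome between intervention and control groups", and "For categorical outcome variables it will be differences in the change in the proportions of children in each category". No exception is made for instruments without a baseline.

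The Outcome measures section places baseline within 3 months of trial entry. Table 1 has three timing columns: Entry, Annual and School. Several instruments have a blank Entry cell, among them the "Child behaviour checklist" under Hypothesis 1c and the Woodcock Johnson tests of "Literacy and numeracy" under Hypothesis 1b.

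**The concern.** A change from baseline needs the same instrument at entry and at follow-up. Many of the child tests have a minimum age, and children enter between 0 and 3 years, so several tests start only at a later wave. A single change-score rule does not fit that measurement schedule.

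The stated aim is school readiness, with benefits hypothesised at the end of the intervention and six months into school. IQ, vocabulary, literacy and numeracy, and behaviour problems are close to that aim, and the instruments for them at school are ones without an entry score. Whoever analyses them must depart from the published rule, and the article does not say how. Hotelling tests are also planned for groups of outcomes. Any group that includes one of these instruments cannot be tested jointly on the change scale.

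**Working it through.** The article gives no figure on this point to reproduce. The check sets the Data analysis rule against Table 1 and then against the stated age ranges.

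**Step 1: count Table 1.** There are 21 instrument rows: 12 under Hypotheses 1a to 1c and 9 under Hypothesis 2. Two, the Greenspan chart and the Alarm baby distress scale, are taken at Entry only. That leaves 21 − 2 = 19 with follow-up. Those without an Entry mark are:

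| Instrument | Hypothesis | Entry | Annual | School |
|---|---|---|---|---|
| WPPSI | 1a | – | X | X |
| Peabody Picture Vocabulary | 1a | – | X | X |
| Child health questionnaire | 1a | – | X | X |
| Expressive Vocabulary Test | 1a | – | X | X |
| Woodcock Johnson | 1b | – | – | X |
| Child behaviour checklist | 1c | – | X | X |
| Story stem | 2 | – | X | X |

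So 7 of 19 (37%) have no change score at any wave, and 19 − 7 = 12 do have one at some wave.

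**Step 2: the school wave.** Sixteen instruments are taken at school.

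- Hypotheses 1a to 1c: 8 instruments. Only the LSAC health items and DECA have an entry score, so 2 of 8.
- Hypothesis 2: 8 instruments. All but the story stem have an entry score, so 7 of 8.
- Total: 2 + 7 = 9 of 16.

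BSID has Entry and Annual marks but no School mark, so it gives a cognitive change to the annual waves only.

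**Step 3: age ranges of SSP and BITSEA.** Both have Entry and Annual marks, but Table 1 gives valid ages of 8–30 months (SSP) and 12–36 months (BITSEA). Let *e* be age at entry in months, *b* the delay to baseline (0 to 3, from Outcome measures) and *t* the follow-up month counted from entry (from Design). For a valid range *L* to *U*, a change score needs *e + b ≥ L* and *e + t ≤ U*. With *b* at its maximum of 3, entry age must satisfy *L − 3 ≤ e ≤ U − t*.

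| | t = 12 | t = 24 | t = 36 |
|---|---|---|---|
| SSP (L = 8, U = 30) | 5 to 18 | 5 to 6 | none (5 ≤ e ≤ −6) |
| BITSEA (L = 12, U = 36) | 9 to 24 | 9 to 12 | none (9 ≤ e ≤ 0) |

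At 24 months the usable entry ages span at most 1 month (SSP) and 3 months (BITSEA), out of an eligible span of 36. At 36 months there are none. Among the instruments listed under Hypothesis 1c, no change score is then available at 36 months or at school: BITSEA is out of range or not taken, the behaviour checklist has no entry score, and the other two are Entry only.

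**Step 4: internal wording.** The Data analysis section speaks first of a difference in mean outcomes, which could be computed for all 19 instruments. The next two sentences turn this into differences in changes, which can be computed for 12 at most.

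**The case against.** *The section already allows a comparison of mean outcomes.* Read alone, that sentence would cover all seven instruments. It does not stand alone, since the sentences for continuous and categorical outcomes both restate it as a change. What stands is that the section is inconsistent and that one side of it points to the right solution.

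*An article leaves such detail to the analysis plan.* That would answer a silence. Here the article states a general rule that its own measurement table cannot support.

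*The tests are age-limited, so no baseline was possible.* For many children this is true and explains the blanks. It is a reason not to state a change score as the universal rule.

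*Most instruments are unaffected.* This stands: 12 of 19 support a change at some wave, and most parent measures do so at school. DECA, listed under Hypothesis 1b, includes a self-control subscale and has Entry, Annual and School marks, so behavioural regulation is not wholly without a change score.

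A reader might infer more than the documents support:

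- *That the trial cannot estimate its effect on IQ or achievement at school.* It can, by comparing follow-up scores. Only the estimate as worded is unavailable.
- *That the trial's primary outcome is affected.* The article names no primary outcome. The closeness of these measures to school readiness is an inference from the stated aim, and the sample size used IQ at 18 and 48 months, not at school.
- *That no child at all can have a 24-month SSP or BITSEA change.* That holds for SSP if baseline is taken on the day of entry. The 3-month baseline window admits the narrow bands shown above.
- *That a 12-month reading will be used as baseline, or BSID subtracted from WPPSI.* Neither is proposed, and the definition of baseline in Outcome measures rules out the first.

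**Conclusion.** The concern holds, limited to the instruments and waves named. The change-from-baseline rule cannot be applied to 7 of the 19 instruments with follow-up, which removes IQ by WPPSI, vocabulary, achievement and the behaviour checklist from the stated analysis at every wave. At school it can be applied to 2 of 8 child instruments and 7 of 8 Hypothesis 2 instruments. For SSP and BITSEA it reaches only a narrow band of entry ages at 24 months and nobody at 36 months.

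The counts rest on Table 1 as printed. The age-band result assumes that annual assessments fall exactly 12, 24 and 36 months after entry and that the stated age ranges are observed. No assumption about the distribution of entry ages is needed. The fault lies in how the estimate is defined and worded. It is not a loss of data and does not invalidate the randomised comparison.

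**What to change.** Amend the Data analysis section to say:

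- For an instrument with no entry score, impact is the between-group difference in follow-up scores, adjusted for age and, where available and age-valid, for an entry measure from the nearest domain (for example BSID for WPPSI, vocabulary and achievement).
- For an instrument with an entry score, the change score may stay, or the follow-up score may be adjusted for the entry score. Nothing in this point requires change scores to be abandoned there.
- A reading taken at 12 months or later is not used as baseline. The existing window of 3 months from entry is unaffected.
- Age-limited instruments such as SSP and BITSEA are compared only at waves where the child is within the valid range.
- The sentence on mean outcomes and the sentences on changes are reconciled, so that each instrument has one stated estimate.

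The entry covariate needs its age-valid condition because BITSEA, for instance, is out of range for infants under 12 months. The cost is analysis wording only. All the measures involved are already in the collection schedule.

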### Sample size and power calculations

The sample size has been determined taking into account both the numbers of observations needed to have sufficient power to detect likely effect sizes and the capacity of the CPS childcare centre where EYEP is being implemented. There is no previous Australian study of an intervention similar to EYEP, therefore calculation of the required sample size has been done using impact sizes estimated for the Abecedarian project. Impact sizes from the Abecedarian project are above those for most other early years programs
[21], however, this can be attributed to its being an extensive and long-term intervention. The similar scale of intervention in EYEP makes Abecedarian an appropriate benchmark for this study. We use impact estimates from the Abecedarian project for IQ at 18 months and at 48 months (
[35] page 1918).

The sampsi routine in STATA was used to calculate the necessary sample size. When type one error is set at 0.05 and type two error set at 0.1 (power = 0.9), the minimum required sample size (per group) is 12 children based on the impact on IQ at 18 months IQ and 19 children based on the impact on IQ at 48 months. We then adjust this required sample size in two ways. First, we take into account that our sample will include families with multiple children. Based on the sample from the pilot phase of EYEP we estimate the number of children per family to be 1.35. We assume perfect correlation of outcomes between siblings which therefore requires expanding the minimum sample size by 1.35. Second, we incorporate an estimated attrition rate of 20 per cent per annum for the intervention and control groups (including item non-response). These adjustments result in a minimum sample size per group of 32 children. Hence it is expected that the sample size of 45 children in intervention and control groups will comfortably meet sample size requirements. It also provides a margin of safety in case standard errors in estimates of the impact of EYEP are larger than for the Abecedarian trial. All children in the Abecedarian trial were enrolled prior to reaching 6 months of age, while children recruited into the EYEP trial have been from a broader range of ages, up to 3 years. To the extent that age of enrolment is a source of variability in impact sizes, our estimates of impact size may therefore have larger standard errors than the Abecedarian study.

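### The unadjusted change-score comparison gives up precision against a baseline-adjusted model, does not match a sample size that reads as based on attained IQ, and cannot be computed for outcomes with no entry measurement

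*Protocol article*

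**What the plan says.** The Data analysis section of the protocol article defines the comparison as change from baseline at each data collection. For continuous outcomes it states: "For continuous outcome variables this will be the difference in mean changes in the outcome between intervention and control groups". The sentence just before describes the same comparison in terms of attained scores, saying it should be possible to "estimate the program impact as the difference in mean outcomes between those groups". On testing it says: "Statistical significance will be established via t-tests for individual outcomes or Hotelling T tests for groups of outcomes". No baseline or age adjustment is mentioned.

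The section on sample size and power gives the basis of the calculation: "We use impact estimates from the Abecedarian project for IQ at 18 months and at 48 months". It reports the minimum per group as "12 children based on the impact on IQ at 18 months IQ and 19 children based on the impact on IQ at 48 months", at a type one error of 0.05 and power of 0.9. It multiplies by 1.35 for siblings, allows for 20 per cent attrition a year, and arrives at 32 per group against a planned 45. No change-score SD and no entry-to-follow-up correlation appears. The same section comments on entry age, which runs from 0 to 3 years: "To the extent that age of enrolment is a source of variability in impact sizes", the standard errors may be larger than in the benchmark trial.

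Table 1 marks no entry measurement for the WPPSI, Peabody Picture Vocabulary, Expressive Vocabulary Test, Child health questionnaire, Woodcock Johnson tests, Child behaviour checklist or Story stem assessment. The cognitive measure at entry is the Bayley.

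**The concern.** Three things do not fit together.

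- **Precision.** Subtracting the baseline forces its coefficient to be 1. When the entry score predicts the follow-up score only weakly, the subtraction adds noise. That is plausible for some outcomes here, since entry may be in infancy and follow-up runs three years and into school. Centre capacity helped to set the sample size, so lost precision is hard to recover by recruiting.
- **Match with the sizing.** The calculation reads as a comparison of attained IQ, but the stated test is on change. The two have the same variance only at r=0.5.
- **Feasibility.** For seven Table 1 instruments the stated change does not exist. Table 1 gives a lower age limit for five of them, so the gap follows largely from the instruments. The analysis rule has to allow for it.

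**Working it through.** **Inputs from the document.** Base n per group 12 (18 months) and 19 (48 months); type one error 0.05, taken as two-sided; power 0.90; sibling factor 1.35; attrition 20% a year; 45 planned per group.

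**Assumed.** Correlation r (not in the document; 0.2 to 0.8 shown, higher values as a check), equal SDs at entry and follow-up, 1:1 allocation, a common slope.

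**The plan's own figure.** 19 × 1.35 / 0.8 = 32.06, so the stated 32 is reproduced with one year of attrition on the 48-month figure. The reading is not unique: 12 × 1.35 / 0.8³ = 31.6 also gives 32. The base figures of 12 and 19 cannot be checked, because the source means and SDs are not given. By the normal approximation, 19 per group implies a standardised effect of d = (1.960 + 1.282) × √(2/19) = 1.05.

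**Variances relative to a comparison of follow-up levels.**
- Change score: 2(1−r)
- ANCOVA on the entry score: 1−r²
- Ratio, ANCOVA to change: (1−r²) / [2(1−r)] = (1+r)/2

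**Sample size.** Multiply 19 by the relative variance and round up. For the enrolled number, multiply 19 by the relative variance, then by 1.35/0.8.

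| r | Change variance | ANCOVA variance | Ratio | n, change | n, ANCOVA | Enrolled, change | Enrolled, ANCOVA |
|---|---|---|---|---|---|---|---|
| 0.2 | 1.60 | 0.96 | 0.60 | 31 | 19 | 51.3 | 30.8 |
| 0.3 | 1.40 | 0.91 | 0.65 | 27 | 18 | 44.9 | 29.2 |
| 0.5 | 1.00 | 0.75 | 0.75 | 19 | 15 | 32.1 | 24.0 |
| 0.7 | 0.60 | 0.51 | 0.85 | 12 | 10 | 19.2 | 16.4 |
| 0.8 | 0.40 | 0.36 | 0.90 | 8 | 7 | 12.8 | 11.5 |

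**Power at d = 1.05 with 45 enrolled and three years of 20% attrition.** The effective number per group is m = 45 × 0.8³ / 1.35 = 17.07. Power is Φ(d√(m/(2v)) − 1.960), with v the relative variance. A level comparison (v = 1) has power 0.87.

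| r | Change | ANCOVA |
|---|---|---|
| 0.2 | 0.68 | 0.88 |
| 0.3 | 0.74 | 0.90 |
| 0.5 | 0.87 | 0.94 |
| 0.7 | 0.98 | 0.99 |

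**Finite-sample check.** Simulated variance ratio, ANCOVA to change. ANCOVA used the entry score plus an age term unrelated to the outcome (20,000 replicates).

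| r | 17 per arm | 27 per arm | 45 per arm |
|---|---|---|---|
| 0.3 | 0.70 | 0.68 | 0.66 |
| 0.5 | 0.81 | 0.79 | 0.77 |
| 0.7 | 0.91 | 0.88 | 0.87 |
| 0.9 | 1.01 | 0.99 | 0.97 |
| 0.95 | 1.04 | 1.02 | 1.00 |

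At r=0.98 the ratio is 1.05 with 17 per arm and about 1.02 with 45. ANCOVA therefore loses by a few per cent at most, and only at r of about 0.9 or more.

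**The case against.** The case for leaving the plan alone has real parts.

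- **The gain depends on r, which is unknown.** This stands. Above r=0.5 the change score beats a level comparison and the sizing is conservative. At r=0.8 ANCOVA saves only 10%. Table 1 includes repeated parent and home scales at 12-month intervals, where r may be high.
- **Equal SDs are assumed.** This stands too. Different SDs would alter the tabulated ratios.
- **The 27 per group is hypothetical for IQ itself.** The WPPSI has no entry value, so the figure could describe only a change on the Bayley. That is correct, but it exposes the second defect: the stated estimator does not exist for the table's intelligence scale.
- **Covariate adjustment is commonly left to an analysis plan, and this is a condensed article.** That would answer a complaint about silence. Here the estimator and the test are both stated.

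Four stronger readings are tempting but not supported. A reader might infer that the analysis is biased or invalid; under randomisation it is not. A reader might infer that ANCOVA can never be less precise; that holds in large samples, and the check above shows small exceptions. A reader might take the remark on entry age as an admission of noise left unadjusted. The text speaks of variability in impact sizes, which is effect heterogeneity. A main-effect age term does not address that and helps only where age predicts the score. Finally, a reader might conclude that the trial is underpowered. The document does not give r, and at r=0.3 the requirement with one year of attrition is 44.9, still within 45.

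**Conclusion.** The point holds as one of lost precision, a mismatch with the sizing, and a rule that cannot be applied to some outcomes. With equal SDs, ANCOVA has 0.60 to 0.90 of the variance of the change score for r from 0.2 to 0.8, before any gain from age. If the trial was sized on attained IQ, the 19 per group understates what a change-score test needs whenever r is below 0.5. At r of about 0.3 the whole margin between 32 and 45 is gone. That basis is the natural reading, but it cannot be confirmed because the source figures are not in the document. The absence of an entry measurement for seven Table 1 instruments depends on no assumption. The change should be made, but the planned comparison is not invalid without it.

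**What to change.** In the Data analysis section, make the primary analysis of each continuous outcome a linear model of the follow-up score on arm, with these terms:

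- the entry score on the same instrument where Table 1 collects it, or a related entry measure named in advance where it does not (for example the Bayley for the WPPSI);
- age at entry as a prognostic covariate. Age at assessment need not be added, since visits at fixed intervals after entry make the two ages nearly collinear;
- standard errors that account for family, because siblings share an allocation.

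Keep the unadjusted change as a supportive analysis where it can be computed, and remove the conflict between describing the effect as a difference in outcomes and as a difference in changes.

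The cost is one or two degrees of freedom and the advance choice of a substitute baseline for each instrument that lacks one. No new data are needed.

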### Randomisation

After recruitment, a family is randomly assigned into either the EYEP participation group (intervention) or usual care group (control). Randomisation is done at arms-length. The random allocation into either the intervention or control group by order of recruitment into the trial is done by [name], who then provides this information to Associate [name] in sealed opaque envelopes. When a family consents to participate in the trial the SRC calls the office of Associate [name] to have the envelope opened that will reveal the status of that participant. This is done in the presence of the family whose child is being randomised.

Blocked randomisation with a variable block size is being applied to conduct the random draw using the STATA sampling without replacement procedure. In families with multiple children participating in the trial all those children will be assigned to either the treatment or control group. When a new sibling of a participant is born during the recruitment phase, the SRC will determine current eligibility of the new sibling by liaising with family services or the child protection worker. When the eligibility conditions for participation in the trial are met, then the parent is invited to consent for the new infant to participate in the EYEP trial. New siblings recruited in this way are automatically allocated to the group (treatment or control) to which their older sibling has been assigned.

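### Families are randomised, but significance is set by child-level t and Hotelling tests with no allowance for family clustering, so the nominal 5% level is not held

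*Protocol article*

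**What the plan says.** Three sections of the protocol article bear on this.

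- **Randomisation.** The family is the unit allocated: "In families with multiple children participating in the trial all those children will be assigned to either the treatment or control group". Siblings born during recruitment are not randomised separately: "New siblings recruited in this way are automatically allocated to the group (treatment or control) to which their older sibling has been assigned".
- **Sample size and power calculations.** Dependence between siblings is acknowledged. From the pilot, "we estimate the number of children per family to be 1.35", and then: "We assume perfect correlation of outcomes between siblings which therefore requires expanding the minimum sample size by 1.35".
- **Data analysis.** The intention-to-treat effect is assessed "at the level of the individual child", as a difference between arms in change from baseline. On inference the section says: "Statistical significance will be established via t-tests for individual outcomes or Hotelling T tests for groups of outcomes". It mentions no family-level analysis, clustered standard error or family random effect.

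**The concern.** An ordinary two-sample t-test or Hotelling test takes its standard error from the number of children and treats them as independent. Here siblings share an arm by design, and the sample size section takes their outcomes to be identical. The effective number of independent units is then nearer the number of families than the number of children. Standard errors come out too small, intervals too narrow and false positives too frequent.

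The larger sample does not repair this. Multiplying the sample by 1.35 buys back power lost to clustering. A test that ignores clustering still has the wrong size, however many families are recruited.

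The same tests are to be used after the 12, 24 and 36 month collections and after school entry, and the impact estimates feed the benefit-cost ratio. The difference in means is not itself invalidated; its stated precision is.

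**Working it through.** **Inputs from the protocol article.** Mean children per family 1.35; sibling correlation 1; type I error 0.05 and power 0.9 (sidedness not stated, two-sided assumed); base requirement "12 children based on the impact on IQ at 18 months IQ and 19 children based on the impact on IQ at 48 months"; attrition 20% per annum; 45 children per group.

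**Assumed.** The family-size distribution is not given. I take 65% of families with one child and 35% with two (mean 0.65 × 1 + 0.35 × 2 = 1.35). Sibling correlations below 1 are also my assumption, to show the range.

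**The protocol's own figure.** 19 × 1.35 / (1 − 0.20) = 25.65 / 0.80 = 32.06, which reproduces the stated minimum of 32 per group. The base figures 12 and 19 cannot be rebuilt, because the IQ effect and SD are not given.

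**Design effect for a child-level mean.** With family size m and sibling correlation ρ, DE = 1 + (E[m²]/E[m] − 1) × ρ. Here E[m²] = 0.65 × 1 + 0.35 × 4 = 2.05 and E[m²]/E[m] = 2.05/1.35 = 1.519.

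**True size of a nominal 5% t-test that ignores families.** Size = 2 × (1 − Φ(1.96/√DE)).

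| ρ | DE | True size |
|---|---|---|
| 0.2 | 1.104 | 6.2% |
| 0.3 | 1.156 | 6.8% |
| 0.5 | 1.259 | 8.1% |
| 1.0 | 1.519 | 11.2% |

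At ρ = 1 a nominal 95% interval therefore covers about 100 − 11.2 = 88.8%.

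**Sensitivity to family size at ρ = 1.** For whole-number family sizes averaging 1.35, a mix of ones and twos gives the smallest E[m²], so 11.2% is the lowest value under perfect correlation. With 72/21/7% of families having one, two and three children, DE = 1.622 and the size is 12.4%. Using 1.35 itself as the design effect gives 9.2%, but that would need every family to have exactly 1.35 children.

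**Simulation under the null** (45 children per arm, 65/35 split, outcomes mutually independent, 10,000 runs):

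| Test | ρ = 0.2 | ρ = 0.5 | ρ = 1 |
|---|---|---|---|
| Child-level t | 6.5% | 8.3% | 11.0% |
| Child-level Hotelling, 3 outcomes | 7.2% | 10.1% | 16.8% |
| Child-level Hotelling, 5 outcomes | 7.4% | 11.9% | 20.6% |
| t on family means | 5.2% | 5.0% | 4.9% |
| Hotelling on family means, 3 outcomes | 5.4% | 5.3% | 5.1% |
| Hotelling on family means, 5 outcomes | 5.0% | 5.3% | 4.7% |

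A separate set of 4,000 runs gave 15.9% and 19.8% for the child-level Hotelling test at ρ = 1, and 10.1% and 10.8% at ρ = 0.5. The simulated t-test agrees with the formula, the Hotelling test is inflated more, and both tests hold about 5% on family means.

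**Effect on the sample size.** For a child-level mean under perfect correlation the factor would be 1.519 rather than 1.35: 19 × 1.519 = 28.9 instead of 25.65 before attrition. With the protocol's own attrition step, 28.9 / 0.80 = 36.1, still below 45.

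**The case against.** The strongest reply is that the Data analysis section names tests and a level of effect but no variance estimator. A t-test can be built on a family-clustered standard error, the authors clearly knew of sibling dependence, and an analysis plan that is not shown may deal with it. A reader might infer that the authors decided to treat siblings as independent; the text does not say so. What stands against the reply is that the section does fix a child-level comparison and names its tests. An analysis plan would have to change that statement, not merely fill a gap.

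Second, perfect correlation is a cautious planning assumption about outcomes, whereas the tests are on changes from baseline. A stable family component cancels in a change score, so the correlation that matters may be lower. This stands, and it is why the result is given as a range. The size still exceeds 5% at any positive correlation.

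Three stronger readings are tempting but not supported:

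- *One error rate for both tests.* The t-test figures do not describe the Hotelling test, and none of the figures holds without an assumed family-size split and correlation.
- *Parent and home measures simply count a two-child family twice.* The article does not say how these measures enter the analysis. HOME partly concerns the parent's response to the particular child. Assessments are timed from each child's entry, so siblings who join at different times may bring parent scores from different dates: correlated, but not duplicates. The point is clearest for the K6 and the depression screener, which measure the parent alone.
- *The trial is too small because 1.35 is the wrong factor.* By the protocol's own method the requirement stays below 45 per group.

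**Conclusion.** The concern holds for the stated analysis. The protocol article randomises families and assumes perfect sibling correlation when sizing the trial, then fixes child-level tests that make no allowance for either, so followed as written they do not hold 5%.

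- **t-test:** about 11% under the protocol's own perfect-correlation assumption with families of one or two children, and about 6 to 8% if the sibling correlation of the change scores is 0.2 to 0.5.
- **Hotelling test:** about 17 to 20% at correlation 1 and about 10 to 12% at 0.5, for three to five mutually independent outcomes.

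The mismatch between the sections is plain in the text and does not depend on these numbers. The sizes rest on the assumed 65/35 split, on the correlation and, for Hotelling, on independent outcomes. The sample size conclusion is not overturned.

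**What to change.** Add to the Data analysis section a statement such as: *Inference will take the family as the unit of randomisation, with siblings who join later counted in their family. Treatment effects will be tested using [one of: family-clustered standard errors with a small-sample correction; a mixed model with a random family intercept; t and Hotelling tests on family means]. Measures of the parent alone (K6, depression screener) will enter once per family at each wave.* One option should be chosen in advance. Because siblings may have different entry dates, the text should also say which assessment supplies the parent score.

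Hotelling T can stay if applied to family means. A permutation test that re-randomises families is an option, not a necessity.

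The cost is a few sentences, a little programming and somewhat wider intervals. At correlation 1 with the 65/35 split, the correct standard error of the child-level difference is about √1.519 = 1.23 times the naive one; at 0.5 it is √1.259 = 1.12 times. No new data and no change to recruitment are needed.
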